**Sample size calculation**

This is done for the primary endpoint. Based on previous studies, we anticipated a 25% reduction of mortality among patients with sepsis and respiratory dysfunction, treated with clarithromycin. To detect this difference with a type-I error of 0.10 and a type-II error of 0.8 and anticipating a 10% loss to follow-up, 55 patients need to be enrolled in each study arm.

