| **Primary study endpoint** | To assess the impact of intravenously administered clarithromycin as adjunctive treatment to standard antibiotic therapy compared to placebo on all-cause 28-day mortality. |
| **Secondary study endpoints** | To assess the effect of clarithromycin treatment compared to placebo treatment on the following:   - 28-day mortality in the subgroup of patients with septic shock - All-cause 90-day mortality - Early sepsis response, defined by an at least 25% decrease of day 1 SOFA score on day 3 - Sepsis response; this is defined by an at least 25% decrease of day 1 SOFA score on day 7 - New sepsis episode until day 28. A new sepsis episode is noted in any patient who experiences at least 25% decrease of day 1 SOFA score on day 7 and who has further increase of day 7 total SOFA by at least 2 points, consequent to infection - Time until new sepsis episode. A new sepsis episode is noted in any patient who experiences at least 25% decrease of day 1 SOFA score on day 7 and who has further increase of day 7 total SOFA by at least 2 points, consequent to infection - Biomarkers of sepsis-induced immunosuppression through genome, transcriptome, metabolome, microbiome and cell population analysis - Cost-effectiveness analysis of clarithromycin against placebo in the study population |
| **Sample size calculation** | This is done for the primary study endpoint. We are planning a study of independent cases and controls with 1 control per case. Prior data indicate that 28-day mortality among placebo-treated patients with sepsis and respiratory dysfunction was 55% and that this was decreased to 30% in patients receiving clarithromycin. We need to study 55 subjects into each group to be able to reject the null hypothesis that the failure rates for both groups are equal with probability (power) 0.8. The Type I error probability associated with this test of this null hypothesis is 0.10. We will use a continuity-corrected chi-squared statistic or Fisher’s exact test to evaluate this null hypothesis. |

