**POWER CALCULATION**

This is done for the primary study endpoint. We are planning a study of independent cases and controls with 1 control per case. Prior data indicate that the mortality among placebo-treated patients with sepsis and respiratory dysfunction was 55% and that this was decreased to 30%^11^. We need to study 55 subjects into each group to be able to reject the null hypothesis that the failure rates for both groups are equal with probability (power) 0.8. The Type I error probability associated with this test of this null hypothesis is 0.10. We will use a continuity-corrected chi-squared statistic or Fisher’s exact test to evaluate this null hypothesis.

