**STATISTICAL ANALYSIS**

Qualitative endpoints will be analyzed by the Fisher’s exact test or continuity corrected Chi- square test, as appropriate. Logistic regression models will be used to evaluate variables associated with 28-day mortality. The effect on sepsis-induced immunosuppression will be a composite endpoint and it will result from the bioanalysis of gene expression, circulating cytokines and stimulated cytokines of patients. More precisely, bioanalysis of gene expression is anticipated to provide pathways modulated by treatment. These pathways will be validated by measurement of representative cytokines in cell supernatants. Comparisons of over-time changes will be done between the two groups of treatment. A p - value lower than 0.05 will be considered statistically significant, unless stated otherwise.

For the cost analysis, cost of each intervention will be counted and compared between groups, with non-parametric Mann-Whitney test, as previously described^10^. This analysis will be subject to robustness control to assess potential differences between different methods of cost calculation. Cost-effectiveness will be expressed as an incremental cost-to-effectiveness ratio (ICER) of clarithromycin compared with placebo, in a within-trial analysis (90 days). The ICER will be compared to a willingness-to-pay factor, which is either defined by the National Institute for Health and Care Excellence threshold or by per capita Gross Domestic Product. ^19, 20^

To evaluate the variation and significance of the ICER estimate, a bootstrapping method will be used.

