**General principles**

- This analysis plan and the primary manuscript will include clinical data up to 90 days, transcriptomic and cell population (by flow cytometry) analyses; the entire cost-effectiveness analysis, cytokine analysis (including serum cytokine concentrations and cytokine production from supernatants of ex-vivo stimulated peripheral blood mononuclear cells-PBMCs) and microbiome analysis will be reported separately.
- Regarding flow cytometry analysis (including cell population and HLA-DR analysis), only samples from patients enrolled in sites proximal to the central lab (Athens) could be included in the current study.
- Regarding trasncriptomic analysis, only a subset of sample sequencing could be covered by the study funding at the time of the present statistical analysis plan. Thus, it was decided to only include in the primary manuscript samples from the subgroup of patients of extremely high severity (within the highest quartile of baseline SOFA score), to demonstrate differences between death and survival. The entire transcriptomic analysis, combined with metabolome, cytokine and microbiome analysis will be reported separately.
- All p-values will be two-sided and the level of significance will be <0.05.
- No interim analysis is planned.
- Regarding clinical data, cell populations and HLA-DR measurements, no adjustment for multiple comparisons is planned and all secondary outcomes will be viewed as exploratory. For transcriptomic data, statistically significant differences will be defined by Benjamini & Hochberg adjusted probabilities < 0.05 and absolute fold expression ≤−1.5 or ≥1.5.
- Analyses will be conducted primarily by the SPSS statistical software, version 24 (IBM) or later; transcriptomic data twill be analysed in the R statistical framework (Version 3.51, R Core Team 2014. R: A language and environment for statistical computing. R Foundation for Statistical Computing, Vienna, Austria)
- Results will be presented by order of importance, starting with the primary outcome first. Due to the nature of the study, additional exploratory analyses will be performed based on the primary and secondary outcomes, in an effort to identify potential host immune pathways modulated by the study drug.

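### The 55 per arm gives 80% power only at alpha 0.10 with no losses; under the SAP's two-sided 0.05 Fisher test, power is about 69%, or 65–67% with 10% loss

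*Supplement*

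**What the plan says.** **Protocol (final version), Power calculation.** The assumed effect is "Prior data indicate that the mortality among placebo-treated patients with sepsis and respiratory dysfunction was 55% and that this was decreased to 30"%. The trial is to "reject the null hypothesis that the failure rates for both groups are equal with probability (power) 0.8", with 55 per group. On alpha: "The Type I error probability associated with this test of this null hypothesis is 0.10". The test is a continuity-corrected chi-squared or Fisher's exact test. No loss to follow-up is mentioned. The sample-size row of the Synopsis agrees.

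**Protocol, Statistical analysis.** "A p - value lower than 0.05 will be considered statistically significant, unless stated otherwise".

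**SAP, Sample size calculation.** "we anticipated a 25% reduction of mortality among patients with sepsis and respiratory dysfunction, treated with clarithromycin". The sizing, per arm, is stated as: "type-I error of 0.10 and a type-II error of 0.8 and anticipating a 10% loss to follow-up, 55 patients need to be enrolled". The two mortality rates are not restated.

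**SAP, General principles.** "All p-values will be two-sided and the level of significance will be <0.05". The primary outcome is not excepted.

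**SAP, Analyses for the primary outcome.** 28-day mortality is compared as a 2×2 table by Fisher's exact test, by intention to treat.

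**SAP, Missing values and Populations.** No imputation is planned, and data from patients who withdraw consent are excluded. Losses therefore reduce the number analysed.

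**The concern.** The sample size is derived at alpha 0.10, while the SAP's decision rule uses 0.05. The protocol derives 55 per arm without any losses; the SAP keeps 55 and says it already allows for 10%. Both changes lower power, yet the headline power was left alone.

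Two things are at stake. First, the success threshold for the only confirmatory endpoint: a primary p-value between 0.05 and 0.10 is positive under the protocol's power calculation and negative under the SAP's general rule. Second, the reading of a null result, which would be credited with 80% power that the planned analysis does not have.

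The SAP sentence also has two wording faults. Taken literally, a type II error of 0.8 is 20% power. A 25% reduction with no rates beside it can be read as relative, which would be a far smaller effect than the one the trial was sized for.

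**Working it through.** **Inputs.** p₁ = 0.55 and p₂ = 0.30 (protocol); power 0.80 (protocol); alpha 0.10 for sizing (both documents) and two-sided 0.05 for testing (SAP); 1:1 allocation; 10% loss (SAP only); Fisher's exact test (SAP). The documents do not say whether the 0.10 is one- or two-sided; two-sided reproduces their figure.

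**Step 1: reproduce 55.** With p̄ = 0.425, d = 0.25 and z_β = 0.8416:

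m = [z_α√(2p̄(1−p̄)) + z_β√(p₁(1−p₁)+p₂(1−p₂))]² / d²

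n = (m/4)·[1 + √(1 + 4/(m·d))]² (continuity-corrected)

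- Two-sided alpha 0.10 (z_α = 1.6449): m = (1.1499 + 0.5693)²/0.0625 = 47.3. Corrected n = 54.999, i.e. **55**. This matches the protocol exactly, with no loss.
- With 10% loss: 54.999/0.9 = 61.1, i.e. **62** per arm.

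**Step 2: the same formula at the SAP's alpha.**

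- Two-sided 0.05 (z_α = 1.9600): m = (1.3702 + 0.5693)²/0.0625 = 60.2. Corrected n = 67.95, i.e. **68** per arm.
- With 10% loss: 67.95/0.9 = 75.5, i.e. **76** per arm.
- By exact Fisher enumeration, 80% is first passed at 69 analysed per arm (80.4%), so 69/0.9 = 76.7, i.e. 77 enrolled.

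**Step 3: exact power of the planned test.** I enumerated all 2×2 tables under the two binomials and summed the probability of those that Fisher's two-sided test rejects. Ten percent off 55 leaves 49.5, so both 49 and 50 are shown.

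| Analysed per arm | Power at alpha 0.10 | Power at alpha 0.05 | Type II error at 0.05 | P(0.05 ≤ p < 0.10) |
|---|---|---|---|---|
| 55 (no loss) | 80.3% | 68.8% | 0.31 | 11.4% |
| 50 | 74.9% | 66.5% | 0.33 | 8.3% |
| 49 | 74.7% | 64.8% | 0.35 | 9.9% |

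The last column is the chance, if the design assumption is true, that the two alphas give opposite verdicts.

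**Step 4: the effect wording.** A 25% relative reduction would be 0.55 × 0.75 = 0.4125. The corrected formula then needs 177 per arm at 0.10 or 221 at 0.05, and 55 per arm would have about 23% exact Fisher power at 0.05. The SAP must therefore mean 55% to 30%, a 25-point absolute difference.

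**The case against.** **The 10% allowance can nearly be reproduced.** Without continuity correction, n at alpha 0.10 is 48, and 48/0.9 = 53.3, i.e. 54, one short of 55. The SAP's authors may have reached their sentence this way. It remains true that neither the protocol's power calculation nor the SAP's primary analysis names an uncorrected test, and this route still uses 0.10. Even the uncorrected normal approximation gives only 76.3% power at 0.05 with 55 per arm.

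**The decision rule is arguably clear.** The protocol's 0.05 allows exceptions and its power section states 0.10, so the protocol is coherent on its own. The SAP was set after enrolment ended and before unmasking, its 0.05 rule is explicit, and the change is conservative, so the type I error is not inflated. That answers any charge of inflated error. It does not remove the conflict: the SAP repeats 0.10 in its own sample-size paragraph and never says that 0.05 replaces the protocol's figure.

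**The wording slips are minor.** The protocol resolves both. They matter because a reader of the SAP alone cannot reproduce 55.

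**The top of the 65–69% range is the no-loss case.** This is correct; the two cases are kept apart here.

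**Putting 0.31–0.35 where the SAP has 0.8 could suggest the trial was designed for that power.** This is a fair point. The design basis should be recorded separately from the power under the final rule.

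**Conclusion.** The concern holds. Under the planned Fisher test, 55 per arm delivers 80% power only at two-sided alpha 0.10 with complete follow-up. At the SAP's two-sided 0.05, power is 68.8% with all 110 patients analysed and 64.8–66.5% with the SAP's 10% loss. That is a shortfall of about 11 to 15 percentage points against the stated 80%.

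These figures assume the protocol's 55% and 30%, equal arms, losses spread evenly and left out of the test, and that the unadjusted Fisher test decides the primary outcome. The conflict between the two alphas does not depend on those assumptions.

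**What to change.** 1. State one alpha for the primary test in both documents: two-sided 0.05, as in the SAP's General principles. Say that it replaces the 0.10 used for sizing.
2. Rewrite the SAP's sample-size paragraph. Give the effect as 28-day mortality falling from 55% to 30%, 25 percentage points absolute. Record the design basis as it was: 55 per arm, power 0.8 (type II error 0.2), two-sided alpha 0.10, no loss.
3. Then give power under the final rule: about 69% with all 110 evaluable and about 65–67% with 10% loss (type II error 0.31–0.35), by Fisher's exact test at two-sided 0.05. This replaces the type II error of 0.8.
4. Delete the claim that 55 includes a 10% loss. It does not hold under the planned test.

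**Cost.** Wording only: no added patients and no new analysis. The stated power becomes less favourable. The protocol's own section on adherence and amendments requires a signed, approved written amendment for any protocol change, so the protocol edit carries that administrative step. The SAP text can be corrected at once; the SAP says it was set before unmasking and database lock, the right point at which to fix the threshold.

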**Populations**

Analyses will be performed on an intention-to-treat (ITT) basis, including all randomized patients, independently of wheather they received the sudy intervention. The ITT population will enter analysis of the primary and all secondary outcomes. In case of consent withdrawal, all data collected prior to this point will be excluded.

The following subgroups of patients are potentially identified:

- Enrolled inside and outside of the intensive care unit (ICU)
- Enrollement in Greece and in Belgium
- Presence or absence of septic shock
- Presence or absence of acute respiratory dysfunction syndrome (ARDS)
- Extremely high severity, defined as patients within the highest quartile of SOFA score, vs all others.
- Presenting pneumonia, intra-abdominal infection or primary Gram-negative bacteremia
- Presence or absence of a Gram-negative pathogen (among infections with identified pathogen only)
- Adequate vs non-adequate empirical antimicrobial treatment (among infections with identified pathogen only). Empirical antimicrobial treatment (defined as the regimen given within 48 hours from infection onset, when cultures are pending) is considered as adequate when administered at the indicated dose and with penetration to the infected site; provided that the identified pathogen has documented or reasonably suspected susceptibility (e.g. metronidazole for *Clostridioides difficile* infection)
- Per protocol (PP) population, defined by patients receiving the entire intervention (all 4 daily doses)

Subgroup analyses will be performed for mortality outcomes (28-day and 90-day).

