**Randomization and bliniding**

Patients are assigned to clarithromycin or placebo, following a random allocation sequence, with a 1:1 design and by block sizes of 10, stratified per study site. The allocation sequence was generated by an independent statistician prior to the study start and delivered within sealed individual envelopes, labeled per study participant code, to each study site. The envelope is unsealed by the study pharmacist (the only unblinded investigator), to prepare the study drug. All other parties involved (investigators, patients, healthcare providers) are blinded to the study arm.

Study intervention consists in either 1gr of clarithromycin or 20 ml of water for injection (placebo), administered once daily as a ready-to use intravenous solution of 250 ml D/W 5%. The intervention is administered for 4 consecutive days, as soon as possible after enrollment. There is no specific time window from enrollment to study drug administration, which is required to be as soon as logistically possible.

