**Analyses for the primary outcome**

The primary outcome will be assesed on an intention-to-treat (ITT) basis, as a 2x2 contigency table by the Fischer’s exact test, and will be confirmed by logistic regression analysis, adjusted for the following severity variables: Age, gender, CCI, SOFA, APACHE II and adequacy of empirical antimicrobial treatment. In case of high collinearity between the model variables, such as age and APACHE, age and CCI or APACHE and SOFA (assessed by the variance inflation factor-VIF, and correlation), if VIF>2 or Pearson correlation coefficient ≥0.8, then only the variable with the lowest p-value in the univariate regression analysis will be entered in the multivariable model. Multivariable regression analysis will be performed in a forward step-wise manner.

Moreover, the rate of incidence of the primary outcome will be compared between the two arms by the log-rank test and the effect size will be quantified by Cox-regression analysis. Finally, the mean absolute difference in mortality among treatment arms will also be presented, with respective 95% CI and the z-statistic for significance.

- Subgroup analyses, with regards to the primary outcome, are planned according to all the subpopulations identified, as follows: per country; per ward of enrollment (ICU or general ward); per protocol (according to whether the study intervention was complete -all 4 doses received); per presence of septic shock (already present in the protocol); per highest SOFA score (defined as higher or lower than the upper SOFA quartile of the population); per presence of ARDS; per initial infectious site; per adequacy of empirical antimicrobial treatment; and per Gram-negative vs non-Gram negative pathogen, among infections with identified pathogens. Interactions between subgroups and arm of treatment were assessed with Breslow-Day test and confirmed with logistic regression for the primary outcome.

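### The SAP's ITT set drops all data of patients who withdraw consent, and dose completion, which death can prevent, is analysed as a mortality subgroup

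*Supplement*

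**What the plan says.** **ITT and withdrawal.** In the SAP, Populations, the ITT set is described as "including all randomized patients, independently of wheather they received the sudy intervention", and "The ITT population will enter analysis of the primary and all secondary outcomes". The next sentence of the same paragraph reads: "In case of consent withdrawal, all data collected prior to this point will be excluded".

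**Per-protocol.** The subgroup list in that section ends with a "Per protocol (PP) population, defined by patients receiving the entire intervention (all 4 daily doses". Under Randomization and blinding, "The intervention is administered for 4 consecutive days, as soon as possible after enrollment". No provision is made for a patient who dies before the fourth dose.

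**Use.** "Subgroup analyses will be performed for mortality outcomes (28-day and 90-day". The section on the primary outcome includes in its subgroup list "per protocol (according to whether the study intervention was complete -all 4 doses received", and closes that list with: "Interactions between subgroups and arm of treatment were assessed with Breslow-Day test and confirmed with logistic regression for the primary outcome". The section on secondary outcomes repeats the list and the interaction sentence for 90-day mortality.

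**The concern.** An ITT set protects the randomised comparison because nothing after allocation decides who is counted. A rule that removes patients on withdrawal breaks that protection, and withdrawal may be related to arm, for example through an adverse event. The trial is small (55 per arm), so a few removals matter.

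The per-protocol problem is different in kind. Four daily doses can be completed only by someone alive on the fourth day of treatment, and the endpoint is death by day 28. Country, ward and septic shock at enrolment are fixed at baseline; dose completion is not. An interaction between arm and dose completion therefore has no plain reading as effect modification, yet it would be reported beside subgroups that do.

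**Working it through.** **1. The plan's own figures.** The plan gives no number for withdrawals or early deaths. Its rates (55% placebo, 30% clarithromycin) and group size serve as reference. With two-sided alpha 0.10, power 0.80 and mean rate 0.425:

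- Uncorrected n = [1.645·√(2·0.425·0.575) + 0.842·√(0.55·0.45 + 0.30·0.70)]² / 0.25² ≈ 47.3, i.e. 48.
- With continuity correction: (47.3/4)·[1 + √(1 + 4/(47.3·0.25))]² ≈ 55.

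The stated 55 per arm reproduces and is not disputed here.

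**2. What the withdrawal rule costs.** Separate what the rule deletes from what withdrawal makes unavailable anyway.

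| Item | Withdrawal before day 28 | Withdrawal after day 28 |
|---|---|---|
| Day-28 status | Not yet observed; missing with or without the rule unless vital status may be obtained | Observed, then deleted |
| Follow-up time for log-rank and Cox | Deleted; could have been censored at withdrawal | Deleted |
| Day-3 and day-7 SOFA response | Deleted if already recorded | Deleted |
| AEs and SAEs to date | Deleted | Deleted |

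The AE row is an inference: the rule covers all data, and the SAP's section on analysing safety outcomes names no population and no exception. The Missing values section adds no imputation or bounds, and Little's test cannot examine patients whose records have been removed.

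**3. Illustration for the primary test (assumed counts).** A person who withdraws after day 28 was alive at day 28, so the rule deletes a survivor. Take 30/55 against 19/55 deaths:

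- Difference 30/55 − 19/55 = 20.0 points; two-sided Fisher p = 0.055.
- Delete one placebo survivor: 30/54 against 19/55. Difference 55.6% − 34.5% = 21.0 points; p = 0.035.
- Delete one clarithromycin survivor instead: 30/55 against 19/54; p stays at 0.055.

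One deletion can cross the SAP's 0.05 level while the estimate moves by about one point. The counts were chosen near the threshold.

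**4. Per-protocol set (assumed early-death shares).** If a share f of 28-day deaths precedes dose 4 and 28-day mortality is p, then per-protocol mortality is p(1 − f)/(1 − pf), ignoring other reasons for missing a dose.

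- *Planned rates, same f in both arms.* For f from 10% to 40%, placebo falls from 55% to 52.4–42.3% and clarithromycin from 30% to 27.8–20.5%. The difference shrinks from 25 points to 24.5–21.9.
- *No true effect, same f.* The difference is 0.
- *No true effect (55% in both arms), f = 10% placebo and 30% clarithromycin.* 0.495/0.945 = 52.4% against 0.385/0.835 = 46.1%: a false benefit of 6.3 points. Reversing the shares gives a false harm of 6.3 points.
- *Drug prevents only early deaths: 28-day mortality 55% against 45%, early deaths 15% against 5% of patients.* 0.40/0.85 = 47.1% against 0.40/0.95 = 42.1%. A true 10-point difference appears as 5.0.

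**5. The interaction test.** All deaths before dose 4 fall in the incomplete stratum by definition. If that stratum held nobody else, mortality there would be 100% in both arms and its odds ratio undefined. If it also held patients who stopped for other reasons, its odds ratio would depend on the mix of reasons in each arm.

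**The case against.** Several points on the other side are right.

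- *Primary analysis.* A reader might infer that the per-protocol definition biases the main result. It does not: the primary analysis is ITT, and patients who die before dose 4 remain in it. Secondary outcomes are declared exploratory.
- *Immortal time.* A reader might call this a guaranteed bias between arms. Both arms receive four blinded infusions and must survive equally long, and step 4 gives no difference when there is no effect and equal timing. When there is no true effect, a difference arises only if early-death risk differs by arm. The subgroup interaction is more exposed, but is still a secondary test.
- *The incomplete group as mostly early deaths.* The documents give neither early deaths nor other reasons for stopping, so this cannot be claimed.
- *Erased deaths.* It is tempting to say the rule deletes deaths. A patient who withdraws is alive then, so a later death is not among data collected before withdrawal. For withdrawal before day 28, keeping earlier data does not supply day-28 status either.
- *Visibility.* The SAP promises the number of patients entering each analysis step, and the protocol's SAE and SUSAR reporting runs independently of the analysis sets. Exclusions would be partly visible and safety reporting would continue. The contradiction in the ITT definition would remain.
- *Consent terms.* Deletion may be required by a consent form not available here. No such requirement appears in the protocol or SAP sections shown, so the plan should state it if it exists.

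**Conclusion.** The concern stands in two parts of unequal weight.

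The withdrawal rule is the more important. It contradicts the definition of the primary analysis set in the same paragraph and, whenever a patient withdraws, produces a post-randomisation exclusion. Its own cost is recorded SOFA response, time that could have been censored, recorded AEs and SAEs, and day-28 status for withdrawals after day 28. It has no effect if nobody withdraws.

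The per-protocol definition and the dose-completion interaction affect secondary analyses only. Dose completion is a post-randomisation variable partly fixed by death, so neither result can be read like a baseline subgroup.

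The size and direction of both effects are unknown. The Fisher example and every per-protocol figure rest on assumed counts or shares and show what is possible, not what this trial would find.

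**What to change.** **Withdrawal.** Amend Populations so that data collected up to withdrawal stay in the ITT and safety analyses unless the consent terms or a participant's erasure request forbid it. Use vital status after withdrawal where permitted, and otherwise censor at withdrawal in the time-to-event analyses. Report withdrawals by arm, separating any whose data had to be erased.

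**Per-protocol.** Define the set as patients who received every dose scheduled while they were alive, so that death before dose 4 is not counted as non-compliance. Report it as a sensitivity analysis, and remove dose completion from the subgroup and interaction lists for 28-day and 90-day mortality.

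**Cost.** SAP wording only; the data needed are those the protocol already collects. The SAP dates itself before unmasking and database lock, so the change could be made blind at that stage. The one real task is to check that the consent form allows data collected before withdrawal to be kept.
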